### 7.3 Annual safety report

The sponsor will submit, once a year throughout the clinical trial, a safety report to the accredited METC.

This safety report consists of:

- a list of all suspected (unexpected or expected) serious adverse events, along with an aggregated summary table of all reported serious adverse events, ordered by organ system, per study;
- a report concerning the safety of the subjects, consisting of a complete safety analysis.

### 7.4 Follow-up of (serious) adverse events

All (S)AEs will be followed up until they have abated, or until a stable situation has been reached. Depending on the event, follow-up may require additional tests or medical procedures as indicated, and/or referral to the general physician or a medical specialist. SAEs need to be reported till end of study within the Netherlands, as defined in the protocol (see 7.2).

### 7.5 Data Safety Monitoring Board (DSMB) / Safety Committee

An independent DSMB will monitor this trial and consists of several members with expertise in the relevant fields of paediatrics, epidemiology and statistics. The composition of the DSMB is outlined in the DSMB Charter. This document also includes statements regarding conflict of interest by the members of the board and an outline of tasks and responsibilities.

The safety of trial participants is of primary concern for the DSMB. The DSMB will meet to discuss the safety review after the outcome data of the first 400 patients (200 in the control arms and 200 in the intervention arm) and 900 patients have become available. Additional reviews will be conducted at the DSMBs request. The DSMB can advise to terminate the study prematurely in case an interim analysis shows clear harm of either one of the interventions or due to external evidence. A formal interim analysis for efficacy (inferential testing) will not be conducted. The DSMB will not be blinded when first assessing the data.

Criteria on which the DSMB may decide to terminate the trial are described in the DSMB charter (see 'K5. DSMB Charter'). The advice(s) of the DSMB will be sent to the principal investigator and the trial methodologist. Should the principal investigator decide not to fully implement the advice of the DSMB, the principal investigator will send the advice to the reviewing METC, including a note to substantiate why (part of) the advice of the DSMB will not be followed.

## 8. STATISTICAL ANALYSIS

### 8.1 Primary study parameters

The analyses will be performed according to the Intention-To-Treat and Per Protocol principle (as secondary analysis). The primary analysis will estimate the relative risk with 95% confidence intervals and p-values for the primary outcomes, using a generalized linear mixed model with log link and binomial distribution, with random intercepts and random slopes per cluster as appropriate. A significance level of 5% will be used.

Both superiority for the proportion of patients that started antibiotic therapy and non-inferiority for adverse clinical outcome must be shown to conclude the effectiveness of the EOS calculator. The use of EOS calculator will be considered superior when it leads to at least a 15% absolute reduction in the proportion of patients who started antibiotic therapy. We expect 10% neonatal complications in the control group. The use of the EOS calculator will be considered non-inferior when the upper bounds of a 95% confidence interval of the relative risk of complications does not exceed 1.5 (comparable to a 15% complication rate).

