### 3. STUDY DESIGN

**Design:** We will conduct a prospective, cluster-randomized trial. We aim to include 1830 newborns from 10 hospitals in the Netherlands during an 18-month period. Cluster-randomization happens at the hospital level. A cluster is finished when a total of 183 participants are included into the cluster. Once finished, a hospital cannot be randomized again. Participating hospitals provide care up to Level II special care for stable or moderately ill newborns, with annual birth rates between 1200 and 4000 births per year, and all use the Dutch national guidelines to guide antibiotic use in newborns at-risk for EOS.

This cluster randomized design can be used when randomization at individual level is difficult and/or creates possibility for bias. The cluster-randomized study design matches our study objectives perfectly because time for randomization is very restricted due to the immediate need to start antibiotic therapy in some newborns. Furthermore, the clustered approach prevents confusion and contamination between the different protocols being compared, thereby limiting bias. After randomization, the assigned protocol is considered standard care for newborns with suspected EOS within 0-24 hours after birth during the study period in that hospital. This means that the NVK guidelines or the EOS calculator (depending on randomization) will be used for all newborns at risk for EOS (within 0-24 hours after birth) in the particular hospital, independent of study participation. It is noteworthy that every attending physician always has the option to choose for clinical management according to another protocol instead of the assigned protocol.

Newborns who do not meet the inclusion criteria, and develop clinical symptoms (suspected for EOS) >24 hours after birth, the NVK guidelines will be used since the EOS calculator is only validated for use in the first 24 hours after birth. If newborns are eligible for inclusion and attending physicians opt for clinical management not according to the advice of the assigned study protocol, this will be recorded with deviations being noted with accompanying justification in both the electronic health record and the electronic Case Report Form (eCRF). After informed consent is obtained data will be collected and used for analysis, and follow-up data collection will ensue.

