## 4. STUDY POPULATION

### 4.1 Population (base)

Newborns are eligible for participation if they have a postmenstrual age of 34 weeks or more, are 0-24 hours old, and in case at least one EOS risk factor or clinical sign of infection (suspected of EOS) is present within the first 24 hours of life.

Ten centers will include patients (five randomized to NVK guideline, five to EOS calculator use). Each center is supposed to include around 183 patients. Per center there are between 1500 and 2500 live births a year. The number of eligible patients is estimated to be between 300/year (center with 1500 live births/year and 20% suspected EOS) and 500/year (2500 live births/year and 20% suspected EOS). With an average number of patients of 2000 per center, a baseline suspected EOS of 20%, and at least 50% participation rate of eligible patients, the average number of patients per center that can participate in a one-year period is:  $2000 \times 0.2 \times 0.5 \times 1 = 200$  patients. This is more than enough for the needed 183 per center during an 18-month inclusion period. In the Netherlands there are currently no competing trials in this patient population.

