### 4.4 Sample size calculation

Superiority: In the control group we expect 40% antibiotic therapy in newborns at risk for EOS. To reduce this to 25% (reduction 15%) by use of the EOS calculator, (80% power, ICC 0,0025, alpha 0,05, 10 hospitals) a total sample size of 330 is required.

Non-inferiority: In the control group and the intervention group, we expect that 10% of newborn infants will fulfill one of the predefined safety criteria. The non-inferiority margin

is set at 15% (absolute difference 5%). The required sample size is 1640 (per cluster 164) (80% power, ICC 0,0025, alpha 0,025, 10 hospitals). Because both hypotheses regarding superiority (reduction in antibiotic therapy) and non-inferiority (adverse clinical outcome) have to be met, the study sample size equals the largest of the two sample sizes.

The potential drop-out or withdrawal is estimated at 10%. We will include 2x 915 newborn infants (total=1830), which means 183 per cluster. The analyses will be performed both according to the intention-to-treat (ITT) principle and according to a per-protocol (PP) analysis. All participants taking part in the study will be analyzed according to the ITT principle. Protocol deviations will be recorded and participants in whom major protocol deviations have occurred will be excluded from the PP analysis. These analyses will be both performed, since attending physicians are able to opt for clinical management not according to the advice of the assigned study protocol. This will be registered as a protocol violation in the eCRF, with accompanying justification (see chapter 3).

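### The non-inferiority sample size ignores the 8 between-hospital degrees of freedom: the stated 80% power is about 70% for the 5-point margin and about 53% for the RR 1.5 rule

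*Protocol*

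**What the plan says.** Section 4.1 splits the ten hospitals as "five randomized to NVK guideline, five to EOS calculator use". Section 3 makes the allocation permanent: "Once finished, a hospital cannot be randomized again". No hospital contributes newborns to both arms.

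Section 4.4 gives the non-inferiority inputs as "80% power, ICC 0,0025, alpha 0,025, 10 hospitals". It adds that in both arms "we expect that 10% of newborn infants will fulfill one of the predefined safety criteria" and sets an absolute margin of 5 points (10% to 15%). The result is 1640 in total, 164 per hospital, raised to 1830 (183 per hospital) for 10% loss. The superiority co-primary ("80% power, ICC 0,0025, alpha 0,05, 10 hospitals", 40% against 25%) needs only 330, so non-inferiority sets the trial size.

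Section 8.1 estimates the relative risk "using a generalized linear mixed model with log link and binomial distribution, with random intercepts and random slopes per cluster as appropriate". Non-inferiority is declared when the upper 95% confidence bound of the relative risk is no higher than 1.5. The section does not say how intervals and p-values are obtained: it names neither a z or Wald method nor a degrees-of-freedom correction.

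**The concern.** With each hospital in one arm, the treatment effect is a contrast between two sets of five hospitals. Its variance has to be learned from the spread between hospitals within arms, which leaves 10 − 2 = 8 degrees of freedom. A sample size based on normal quantiles treats that variance as known and so overstates power. Both co-primaries must succeed, so a shortfall on this one is a shortfall for the trial.

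The same feature bears on section 8.1. A random slope for treatment by hospital needs treatment to vary within a hospital, which it never does here, and the protocol names no other within-hospital covariate that could carry a slope. If the model were fitted with a program's large-sample default, the interval would be too short. On a safety outcome that error runs in the unsafe direction.

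**Working it through.** **Inputs** (sections 4.1 and 4.4): 5 hospitals per arm; m = 164 per hospital, so 820 per arm; event rate 10% in both arms; margin 5 points; ICC 0.0025; alpha 0.025, read as one-sided. From section 8.1: relative-risk margin 1.5.

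**Step 1. Reproduce the plan's figure.**
- Without clustering: 2 × 0.10 × 0.90 × (1.960 + 0.842)² / 0.05² = 565 per arm.
- Design effect: 1 + 163 × 0.0025 = 1.4075.
- Total: 2 × 565.1 × 1.4075 = 1591, within 3% of the stated 1640.
- Standard error of the risk difference at 820 per arm: √(0.18 × 1.4075 / 820) = 0.01758.
- Margin / SE: 0.05 / 0.01758 = 2.845.
- Normal power: Φ(2.845 − 1.960) = 81.2%.

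The stated 80% is therefore a normal-quantile figure.

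**Step 2. Same standard error, 8 df.** The critical value rises from 1.960 to 2.306. Power comes from the noncentral t with noncentrality 2.845.

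| Scale and size | Margin / SE | Normal power | Power with t, 8 df |
|---|---|---|---|
| Risk difference, 164 per hospital | 2.845 | 81.2% | 70.3% |
| Risk difference, 183 per hospital (no loss) | 2.955 | 84.0% | 73.6% |
| Log relative risk, 164 per hospital | 2.307 | 63.6% | 52.7% |
| Log relative risk, 183 per hospital (no loss) | 2.397 | 66.9% | 55.8% |

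For the relative-risk rows, the standard error at 164 is √(2 × (0.9/0.1) × 1.4075 / 820) = 0.1758, and the distance is ln 1.5 = 0.4055.

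With ten hospitals, 80% power on the risk difference with 8 df would need about 233 analysed per hospital (about 2,330 in total), so 1640 contains no allowance for the few clusters.

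**Step 3. Superiority.** For 40% against 25% at 164 per hospital: SE = √((0.24 + 0.1875) × 1.4075 / 820) = 0.02709, and 0.15 / 0.02709 = 5.54. Power against no difference is 99.8% with 8 df.

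**Step 4. What z intervals would do, if used.**
- Width relative to t on 8 df: 1.960 / 2.306 = 85%.
- Beta-binomial simulation at the boundary (10% against 15%, RR 1.5), ICC 0.0025, 164 per hospital, 40,000 runs, moment-based stand-ins for the mixed model: false non-inferiority 2.9% and 3.6% with z, 2.45% with a cluster-level t on 8 df.
- A separate simulation fitting the log-binomial random-intercept model by maximum likelihood (1,500 runs, Monte Carlo error about 0.5 points): 3.9% with z.
- One stand-in combined with t on 8 df, its variance never allowed below the binomial value, was conservative: 1.5% error and 49% power on the RR scale. The cluster-level t gave 53% power.

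**The case against.** Section 8.1 does not say that intervals are z or Wald. A degrees-of-freedom method is commonly left to a statistical analysis plan, which may exist and is not shown. This stands: a reader might infer that the planned confidence intervals are too narrow, but the protocol only leaves that possible.

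A reader might also combine narrow intervals with 70% power. These are alternatives. With z intervals the error rate is inflated and the t-based power loss does not arise; with t on 8 df the error is controlled and power falls.

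Nor do random slopes shorten the interval. A slope that cannot be estimated is dropped or fails to converge, and the qualifier "as appropriate" lets it be dropped. The slope wording is a specification fault only.

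A reader might infer that false superiority exceeds 5%. A simulated two-sided error of 8.1% at 40%/40% and ICC 0.0025 might suggest it, but only about half of that, roughly 4%, would favour the calculator. It also tests against no difference, whereas section 8.1 asks for a 15-point absolute reduction. Larger inflation appears only at ICCs above 0.0025, which the documents do not give.

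None of this reaches the sample size. Section 4.4 states its power in the protocol itself, and an analysis plan that adopts a valid small-sample method would make that figure wrong.

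**Conclusion.** The point holds for the non-inferiority co-primary. With the protocol's own inputs and an analysis that respects five hospitals per arm, power is about 70% for the 5-point margin (about 74% if nobody is lost), not 80%. Under the relative-risk rule that section 8.1 actually applies, it is about 53%. The fall from 81% to 64% with normal quantiles comes from moving from a difference margin to a ratio margin; the further fall to 53% comes from the 8 df.

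The inflation of false non-inferiority is conditional on z intervals being used, and is modest at the stated ICC (about 3–4% against 2.5%). Superiority power against no difference is not affected.

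These figures assume equal hospital sizes, an ICC of exactly 0.0025, a true 10% rate in both arms, and alpha 0.025 read as one-sided.

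**What to change.** In section 8.1, specify a hospital random intercept only and delete the random slopes. Base the 95% confidence intervals and p-values on t with 8 df, either through between-within degrees of freedom in the mixed model or through a cluster-level analysis of hospital log risks. The simulations favour the cluster-level form, which held its nominal error without being conservative. Any permutation test should be a sensitivity check, restricted to the allocations that the randomization actually allowed.

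In section 4.4, restate non-inferiority power for the analysis and margin actually used: about 70% if the margin is the 5-point difference, about 53% if it is RR 1.5.

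The cost is a change of wording, intervals about 18% wider than z intervals (2.306 / 1.960 = 1.18), and a less favourable stated power. No additional hospitals or newborns are required.

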## SUMMARY

**Rationale:** Newborns are at risk for early-onset, within 72 hours after birth, sepsis (EOS). The incidence of proven EOS is 0.5-2.0 per 1000 live births. For the Netherlands, based on 170,000 births per year, this means approximately 85-340 newborns. However, approximately 5% of late preterm and term newborns are given antibiotics in compliance with current Dutch guideline, which is equivalent to 8,500 newborns per year. An alternative is the CE certified EOS calculator application, which calculates an individual risk of EOS for each newborn with treatment advice.

**Objective:** To investigate whether the use of the EOS calculator safely reduces antibiotic exposure in newborns with suspected EOS compared to the current Dutch guidelines.

**Study design:** A cluster-randomized study design (randomization at hospital level) with 10 hospitals.

**Study population:** Newborns in the first 24 hours after birth, at a gestational age of  $\geq 34$  weeks, with at least one risk factor or symptom consistent with EOS.

**Intervention:** Randomization will take place at cluster level for either the EOS calculator or antibiotics administration according to the Dutch guideline.

**Main study parameters/endpoints:** *Co-primary superiority outcome:* The proportion of patients starting antibiotic therapy started for suspected and, or proven EOS in the first 24 hours after birth. *Co-primary non-inferiority outcome:* The presence of one or more of four predefined safety criteria, namely 1) the need for any respiratory support, and/or 2) the need for an intravascular fluid bolus for hemodynamic instability due to sepsis, and/or 3) referral to a Neonatal Intensive Care Unit for sepsis treatment, and/or 4) proven EOS.

*Secondary endpoints:* The total duration of antibiotic therapy; The percentage antibiotic therapy started for suspected and, or proven EOS if symptoms started between 24-72 hours after birth; Quality of life: To get an impression of the impact of (suspected) EOS on parents/guardians and their child, parents/guardians will be asked to fill in a questionnaire on day 14.

**Nature and extent of the burden and risks associated with participation, benefit, and group relatedness:** This study will have negligible risks and minimal burden.

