The NVK guideline uses risk factors and symptoms to categorically indicate which newborns need antibiotics (11). Evaluating its use in 9 Dutch hospitals, we found limited adherence, especially when antibiotics are recommended by the guideline (13). This limited adherence indicates that it is desirable to amend the current guideline or that the use of an alternative method should be further investigated.

A new method for determining which newborns need antibiotics is the “EOS calculator” (14,15). Developed in the United States, this method uses a combination of detailed information about risk factors and the presence of specific symptoms to calculate an individual risk of EOS for each newborn. The EOS calculator is an algorithm that divides newborns into risk groups with concrete treatment advice (antibiotics, extra observation, normal care). The EOS calculator calculates the risk for an individual newborn using 5 maternal risk factors (gestational age, duration of rupture of membranes, highest intrapartum maternal temperature, use of intrapartum antibiotics, maternal Group B Streptococcus (GBS) colonization status) combined with the newborn’s clinical condition after birth. These data are objective and easy to retrieve, without additional actions.

The EOS calculator has been developed and validated using data of over 600,000 newborns born with a gestational age of 34 weeks or more. A subsequent large-scale implementation study included 204,485 newborns and showed a decrease in antibiotic use from 5.0% to 2.6% (16). EOS incidence and readmissions for EOS did not change after implementation, nor were any other adverse effects observed. The EOS calculator has now been evaluated in more than 20 studies, of which 8 with actual implementation. Meta-analysis shows up to an average of 44% less antibiotic use, without indications of negative consequences (17). Implementation in Tergooi hospital yielded comparable results (18). There are no known implementation studies in which EOS calculator use was not effective or proven unsafe.

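### Section 8.1 makes the 15-point planning effect the pass mark for superiority, so the power in section 4.4 does not apply to the stated rule and a true 15-point reduction passes only about half the time

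*Protocol*

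**What the plan says.** Section 4.4 sets the superiority inputs. The control rate is given as "In the control group we expect 40% antibiotic therapy in newborns at risk for EOS", and the alternative as "To reduce this to 25% (reduction 15%) by use of the EOS calculator". With "80% power, ICC 0,0025, alpha 0,05, 10 hospitals", the result is "a total sample size of 330 is required". The non-inferiority comparison needs 1640 (164 per cluster) and governs the size of the trial; with 10% drop-out the target becomes 1830.

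Section 8.1 specifies a log-link binomial mixed model giving a relative risk with 95% confidence interval and p-value, at a 5% significance level. It requires both co-primaries to succeed. It then gives one decision rule for each. Non-inferiority holds if the upper confidence limit of the relative risk of complications does not exceed 1.5. Superiority is worded in parallel: "The use of EOS calculator will be considered superior when it leads to at least a 15% absolute reduction" in the proportion starting antibiotics.

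The protocol gives no other superiority criterion, and no power for the 15-point rule.

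**The concern.** A planning effect and a success threshold do different jobs. The planning effect is the true difference at which a test of some smaller null value is likely to succeed. If the threshold is set equal to the planning effect, the estimate falls on either side of it about equally often, and more patients do not help.

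Superiority is a necessary condition for the trial's conclusion. A calculator that performs exactly as planned could fail it on close to a coin toss, with a very small p-value beside the failure. Deciding after the results whether 15 points was a rule or only a target would look post hoc.

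**Working it through.** **Inputs.** From 4.4: control 40%, calculator 25%, ICC 0.0025, 10 clusters (5 per arm), two-sided alpha 0.05, power 80%; 1640 analysed, 164 per cluster; 10% complications in each arm. From 8.1: the 15-point rule and the relative-risk limit of 1.5.

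**1. Reproduce the 330.** Two proportions, pooled variance under the null, no continuity correction, mean rate 0.325:

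n per arm = [1.96·√(2·0.325·0.675) + 0.8416·√(0.4·0.6 + 0.25·0.75)]² / 0.15² = 151.9, so 152.

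With m newborns per cluster, 5m = 152·[1 + (m − 1)·0.0025]. This gives m = 151.62/4.62 = 32.8, so 33 per cluster and 330 in total. The power at 330 (design effect 1.08) is 80.2%. A one-sided version gives 260 and a continuity-corrected version 360. The stated figure is therefore a two-sided test of zero difference.

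**2. Standard error at the governing size.** Design effect = 1 + 163·0.0025 = 1.4075. Effective n per arm = 820/1.4075 = 582.6. SE of the difference = √[(0.24 + 0.1875)/582.6] = 0.0271.

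**3. Probability of meeting the 8.1 rule, read on the point estimate.** P(observed ≥ 0.15) = Φ[(true − 0.15)/SE], with the control rate at 40% and the SE recomputed for each true effect:

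| True reduction | SE (N=1640) | P(rule met) | P(significant against zero) |
|---|---|---|---|
| 13 points | 0.0274 | 23% | 99.7% |
| 15 points | 0.0271 | 50% | >99.9% |
| 17.2 points | 0.0267 | 80% | >99.9% |

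At a true 15 points the numerator is zero, so the answer is 50% at any N. A simulation of 200,000 beta-binomial cluster trials gave 51.3% at 330, 50.9% at 1640 and 49.7% at 1830; the small departures come from the discreteness of counts. The same simulations were significant against zero in 80.7%, 99.98% and 99.99% of trials. Every simulated trial that met the 15-point rule was also significant, so adding p<0.05 to the rule changes nothing. With a cautious t reference on 8 degrees of freedom, the test against zero at 1640 still has 99.8% power at 15 points and 98.5% at 13.

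**4. Joint success at the design assumptions.** For complications at 10% in both arms, SE of the log relative risk = √[2·0.9/(0.1·582.6)] = 0.176. Power to keep the upper limit at or below 1.5 = Φ(0.4055/0.176 − 1.96) = about 64%. Under independence, joint success = 0.50·0.64 = about 32%. If superiority were tested against zero, it would be about 64%. The gap between 32% and 64% is due to the superiority rule; the remaining shortfall is due to the non-inferiority limit and is a separate matter.

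**The case against.** The best defence is that a minimum worthwhile reduction is a legitimate condition before a national guideline changes. The rule is conservative: it does not inflate the type I error, bias the estimate or alter the sample size, and the relative risk, interval and p-value are reported whatever the label. This stands. It makes the threshold a choice that may be kept, but the choice needs its own operating characteristics and the protocol gives none. The sentence might also be a loose restatement of the target, but its wording matches the non-inferiority rule beside it, and readers will apply it as written.

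Some stronger readings are tempting, and the document does not support them.

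- *That the stated 80% is false.* It is right for 330 newborns and a zero null. It simply does not describe the rule in 8.1.
- *That the confidence limit must clear 15 points*, which would succeed only about 2.5% of the time at a true 15 points. The non-inferiority rule names a confidence limit; the superiority rule names none.
- *That the control rate is really about 25%, so the rule almost always fails.* A reader might divide "approximately 5% of late preterm and term newborns are given antibiotics in compliance with current Dutch guideline" by "a baseline suspected EOS of 20"%. The first is a national figure, the second a recruitment estimate for the participating hospitals, and about half of eligible newborns are expected to take part. Section 4.4 states 40% expressly for at-risk newborns. At 40%, the literature figure ("Meta-analysis shows up to an average of 44% less antibiotic use") would be 0.40·0.44 = 17.6 points, and the rule would be met about 84% of the time (SE 0.0267).
- *That an absolute rule cannot go with a relative-risk model.* Deriving a risk difference from such a model is ordinary content for an analysis plan, which is not at hand.

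**Conclusion.** The point holds. Section 4.4 sizes a test against zero; section 8.1 decides on a different rule whose threshold equals the planned effect. Under the point-estimate reading, the chance of being called superior at the planned effect is about 50% at any sample size, against more than 99.9% for a test against zero with 1640 newborns. An 80% chance under the rule needs a true reduction of about 17.2 points at that size. Overall success at the design assumptions is about 32%.

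These figures rest on the protocol's 40% control rate, ICC of 0.0025 and 10% complication rate, on normal approximations, and, for the joint figure, on independence of the two outcomes. The 50% depends on almost none of this: only on the threshold equalling the true effect and the estimate being roughly symmetric about it.

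**What to change.** In section 8.1, replace the superiority sentence with: superiority is concluded when the two-sided 95% confidence interval for the relative risk of starting antibiotics lies entirely below 1; the risk difference is reported with its 95% confidence interval and read against 15 points as a benchmark of clinical relevance. Section 4.4 keeps 15 points as the planning assumption.

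This costs one amended sentence and no extra newborns. Its downside should be stated openly: a statistically significant reduction below 15 points would count as superior. At 1640 and a 40% control rate, an observed reduction of about 5.5 points would be enough.

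If the sponsor wants 15 points as a true minimum, it should keep the rule, say that it applies to the point estimate, and restate the power for a true reduction above 15 points, for example about 80% at 17.2 points with 1640 newborns. Either choice should be fixed before comparative outcome data are examined.

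### The non-inferiority comparison is sized on a 5-point absolute margin but decided on a relative risk of 1.5, so at the assumed 10% rate its power is about 64 to 67%, not 80%

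*Protocol*

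**What the plan says.** Section 4.4 expects the same safety-composite rate in both arms: "we expect that 10% of newborn infants will fulfill one of the predefined safety criteria". Of the margin it says that it "is set at 15% (absolute difference 5%). The required sample size is 1640 (per cluster 164" newborns), under these settings: "80% power, ICC 0,0025, alpha 0,025, 10 hospitals". Section 4.1 gives the allocation: "five randomized to NVK guideline, five to EOS calculator use". Allowing for 10% drop-out, section 4.4 enrols 1830, or 183 per cluster. It takes the larger of the two co-primary sample sizes, so this comparison sets the size of the trial.

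Section 8.1 estimates a relative risk from a log-link binomial mixed model. It declares non-inferiority when "the upper bounds of a 95% confidence interval of the relative risk of complications does not exceed 1.5". It describes that limit as comparable to a 15% complication rate, just after giving 10% as the expected control rate. It requires both co-primary results before the calculator is called effective.

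No section gives a power or sample size on the relative-risk scale, or says how a control rate other than 10% would be handled.

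**The concern.** Both the sizing margin and the decision rule are fixed in the protocol, and they are on different scales. A margin of 5 points and a ratio of 1.5 mark the same boundary when the control rate is exactly 10%. The precision of a log relative risk near that boundary is not the precision of a risk difference, so power computed for one does not carry over to the other.

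Two things are at stake. First, a calculator that is truly no worse could miss non-inferiority much more often than the planned one time in five, and the trial's conclusion needs this result. Second, under a ratio rule the absolute excess that counts as acceptable moves with the control rate, whereas section 4.4 presents it as 5 points.

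**Working it through.** **Inputs.** From sections 4.1, 4.4 and 8.1: p = 0.10 in both arms; margin 0.05 (difference) or ln 1.5 = 0.4055 (log relative risk); one-sided alpha 0.025, which matches a two-sided 95% interval; ICC 0.0025; 5 clusters per arm; 164 evaluable or 183 enrolled per cluster. Normal critical values are used throughout.

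**1. Reproducing 1640.** Risk-difference test with the Farrington-Manning variance. The restricted rates at a 5-point difference are 0.0803 and 0.1303.

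- Null SD: √(0.0803×0.9197 + 0.1303×0.8697) = 0.4326. Alternative SD: √0.18 = 0.4243.
- n per arm before clustering: [(1.96×0.4326 + 0.8416×0.4243)/0.05]² = 580.7.
- Cluster size for 5 clusters per arm: m = n(1 − ICC)/(5 − n×ICC) = 580.7×0.9975/(5 − 1.452) = 163.3, so 164, total 1640. This is an exact match.
- The simpler unpooled variance gives 566 per arm and 1580 in total, 3.7% low.
- A relative-risk margin of 1.5 gives about 3,010 (step 4), so it is not the source of 1640.

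**2. Power at 164 per cluster.** Effective n per arm = 820/(1 + 163×0.0025) = 820/1.4075 = 582.6.

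- Difference rule: SE = √(0.18/582.6) = 0.01758; 0.05/SE = 2.845; power = Φ(2.845 − 1.96) = 81.2%.
- Relative-risk rule: SE(log RR) = √(2×0.9/(0.1×582.6)) = 0.1758; 0.4055/SE = 2.307; power = Φ(2.307 − 1.96) = 63.6%.

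A beta-binomial simulation (200,000 runs) gave 81.2% and 63.3%. A restricted-score test of the relative risk gave 63.6%.

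**3. Power with no drop-out.** At 183 per cluster, effective n = 915/1.455 = 628.9; SE(log RR) = 0.1692; power = Φ(2.397 − 1.96) = 66.9% (simulation 66.6%).

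**4. Size for 80% power under the relative-risk rule.** n per arm = 18×[(1.96 + 0.8416)/0.4055]² = 860 after rounding up; m = 860×0.9975/(5 − 2.15) = 301; total 3,010 evaluable. The score test gives 307 per cluster, 3,070 in total.

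**5. The two rules on the same data.** Take observed rates of 10% (control) and 11% (calculator) with 820 per arm.

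- Difference: upper limit = 0.01 + 1.96×√(1.4075×(0.0900 + 0.0979)/820) = 0.045, inside 5 points.
- Relative risk: upper limit = exp[ln 1.1 + 1.96×√(1.4075×(9.00 + 8.09)/820)] = 1.54, outside 1.5.

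The verdicts differ although the control rate is exactly as assumed.

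**6. Other control rates.** These are illustrative assumptions; the protocol gives only 10%. Figures are for 164 per cluster with equal true rates.

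| Control rate | Excess allowed by RR 1.5 | Power of RR rule |
|---|---|---|
| 5% | 2.5 points | 35% |
| 8% | 4 points | 53% |
| 10% | 5 points | 64% |
| 12% | 6 points | 72% |
| 15% | 7.5 points | 83% |
| 20% | 10 points | 93% |

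**The case against.** The best defence is that a ratio margin is legitimate, that section 8.1 is the only decision rule stated, and that at the expected 10% its boundary is correctly described. The protocol says comparable, not equal. All of that stands. The defect is narrower: power was computed for a different rule.

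Several stronger readings are tempting but not supported.

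- **That 1640 is miscalculated.** It is right for a 5-point difference.
- **That an equivalent calculator fails more than one time in three.** At 1640 evaluable the failure rate is 36.4%. If all 1830 are analysed it is 33.1%, just under one in three.
- **That the control rate will probably exceed 10%, because the composite counts any respiratory support.** The protocol gives no figure for oxygen or CPAP use, and section 6.1.1 calls each individual criterion very uncommon. Rates other than 10% are scenarios only.
- **That the rule is both underpowered and lax on safety.** These mostly lie on opposite sides of 10%. Below it the ratio rule is stricter than 5 points and power is poor. Above it the rule is laxer and power recovers, passing 80% by a 15% rate. At 10% the mismatch raises the risk of an inconclusive trial, not of a false safety claim.
- **That power is really nearer 53%.** This requires a t reference on 8 degrees of freedom, which the protocol does not specify. It would also lower the difference rule, to about 70%, so it is a separate matter from the mismatch.

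**Conclusion.** The point holds. The 80% in section 4.4 belongs to a test that section 8.1 does not plan to use. At 10% in both arms and ICC 0.0025, the stated rule has about 64% power at 1640 evaluable and about 67% at 1830, a shortfall of 13 to 16 percentage points. About 3,010 evaluable would restore 80%.

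The 5-point tolerance holds only at a 10% control rate. The shortfall is present at that rate and grows below it. Tolerated harm above 5 points arises only if the control rate exceeds 10%, which the documents neither show nor rule out. These figures assume equal true rates, equal cluster sizes and the protocol's ICC.

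**What to change.** Use one scale for sizing and decision, and settle it before outcomes are seen by arm.

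- **Minimum, if the relative risk of 1.5 is kept.** Restate the power in section 4.4 as about 64 to 67% at a 10% rate. Say in section 8.1 that 1.5 corresponds to 5 points only at a 10% control rate. This costs wording and one less favourable figure. Enlarging the trial instead would need about 301/0.9 = 334 enrolled per centre, against the 2000×0.2×0.5×1.5 = 300 that section 4.1's own recruitment assumptions yield in 18 months.
- **Alternative.** Conclude non-inferiority when the upper 95% limit of the risk difference is below 5 points, with the relative risk as supportive. This keeps 1640 valid at 10%, but it is a trade-off. Power falls above 10%: at 20%, SE = √(0.32/582.6) = 0.0234 and power = Φ(2.133 − 1.96), about 57%. Below 10% it tolerates a larger relative increase: at 5%, a rise to 10%, which is a doubling. It also makes non-inferiority easier to show at the design rate (81% against 64%), so the reason should be documented. Changing a co-primary decision rule may count as a substantial amendment under section 10.3.

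Under either choice, state how a control rate other than 10% will be handled.
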